### Plans to promote participant retention and complete follow-up {18b}

Screening patients to assess their risk of PI within 36h of hospital admission and expected hospital length of stay ≥24h following recruitment and informed written consent (in person or via a proxy) increases participant retention and enables at least one outcome assessment (i.e. assessment of a de-identified photograph by a blinded outcome assessor). Given the busy nature of acute clinical settings, ResNs often visit participants several times a day to collect outcome data.

### Data management {19}

Data are entered directly into REDCap (Research Electronic Data Capture), via a secure web platform for building and managing online databases, by ResNs using a password-protected iPad. The eCRF was adapted from the paper version used in our pilot trial [13].

The data management plan for data that will be retained on completion of the trial is as follows:All data retained will be in an electronic, re-identifiable format (i.e. stored separately from participant identifying information, with only participants’ unique study number documented in both datasets)Paper-based/non-electronic data (e.g. data collection instruments and research materials such as PICFs) will be transferred to an electronic format, and all paper-based/non-electronic data destroyedElectronic data (including re-identifiable raw data sets exported from REDCap, electronic photographs, and research materials such as PICFs) will be securely stored using password-protected computers and/or using Griffith University’s secure cloud storage systems. These data will be stored indefinitely for potential future research use by the research team (in accordance with the NHMRC Australian Code for Responsible Conduct of Research)

Data management plans can be accessed by team members of the CTC and ResNs via the trial protocol and SOP.

### Confidentiality {27}

All participants are assigned a study-specific identification number. Exported data are de-identified and stored separately from the data set containing participant identifying information (only the participant’s unique study number is contained in both files for the purpose of re-identification). eCRFs and any study information are stored on a password-protected computer or secure Griffith University applications accessible only by the research team. All paper copies of study information, including the signed participant consent forms, are stored in a locked cupboard, in a secure room, located at the hospital site where the data are collected. All collected paper-based data are securely stored for the duration of the trial and will be transferred to an electronic format, with paper-based/non-electronic data destroyed once the trial has ended. Re-identifiable electronic data will be securely stored indefinitely for scholarly priority (e.g. secondary analysis) and in accordance with the NHMRC Australian Code for the Responsible Conduct of Research and GCP. Individual participant data (IPD) is not shared outside of the research team as data collected may be potentially re-identifiable. This decision was made as IPD sharing may have discouraged potential participants from agreeing to participate if they were aware their data may be shared with others. De-identified electronic data (i.e. name, date of birth and hospital number removed) will be shared with members of the research team who are located at institutions outside of Australia.

### Plans for collection, laboratory evaluation, and storage of biological specimens for genetic or molecular analysis in this trial/future use {33}

N/A. This trial does not collect biological specimens for analysis.

## Statistical methods

### Statistical methods for primary and secondary outcomes {20a}

The patient is the unit of measurement. The primary outcome, development of a new sacral HAPI, is dichotomous. The main analysis will be based on comparisons of the cumulative incidence of pressure injuries in the two groups. Relative risk (RR) of HAPI for the intervention group compared to the control group will be computed and reported along with 95% confidence intervals and *P* values.

We anticipate that prognostic imbalance of known (e.g. age, BMI, number of comorbidities) and unknown prognostic factors is unlikely between the groups due to central randomisation and treatment concealment. However, if we find any differences, we will conduct adjusted analyses using multiple regression models. We do not expect effect sizes to vary between hospitals, but centre-to-centre variability will be assessed, and cluster-adjusted analysis will be carried out as a form of sensitivity analysis if required. Patients’ declining to participate in the trial are given the opportunity to consent to some non-identifiable data being collected (i.e. admission type, age, sex, and PI risk score). These data will enable us to compare some characteristics of eligible and consenting patients (i.e. participants) versus patients who are eligible but not consenting (i.e. non-participants).

For the secondary endpoints, “time to HAPI” will be analysed using the Kaplan-Meier curve and log rank tests. Hazard ratios along with 95% confidence intervals will be reported. Additional Cox regression models will be used to detect the influence of prognostic factors. As for the “stage of HAPI”, a chi-square test will evaluate if the intervention group differs from the control patients. All data will be entered directly into a web-based data collection tool (REDCap) and then exported into SPSS (V 24). Prior to analysis, a rigorous process of data cleaning to check outlying figures, missing, and implausible data against source data will be undertaken. Sample attrition will be managed via intention-to-treat analysis to ensure an unbiased comparison of the groups by randomisation. An expert biostatistician will lead all analyses.

A parallel economic evaluation from the health system perspective using patient-level data from the trial to compare costs and effects of prophylactic silicone foam sacral dressings in addition to routine care with routine care alone will be undertaken. In the first step, a cost-effectiveness analysis will compare the costs and effects of prevention using the trial primary outcome (cumulative incidence) as the measure of effect. Data collected on costs and clinical outcomes will be used to calculate the incremental cost per sacral HAPI avoided, which is the difference in the mean costs of prevention (i.e. measured to the trial endpoint) divided by the difference in sacral HAPI incidence. In an extended step, a cost-benefit analysis will be undertaken to incorporate the benefits of prevention measured in dollars using data from the extended 28-day follow-up. Benefits will include any difference in costs of sacral HAPI treatment and HLOS between groups (documented on discharge for all participants).

As already described, a parallel process evaluation is being undertaken alongside the trial [16, 17].

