## Methods: participants, interventions, and outcomes

### Study setting {9}

This multi-site RCT is currently taking place at three acute-care public hospitals in Southeast Queensland, Australia. Two of the hospitals are quaternary hospitals and the third, a tertiary facility. All sites have participated in previous clinical trials. For more details, refer to the Australian New Zealand Clinical Trials Registry: ACTRN12619000763145.

Each site is supported by associate investigator (AI) nurse leaders, who provide ongoing clinical expertise and support for the study. We recruit eligible participants from general medical-surgical wards at each site. The inclusion of multiple sites and wards spreads the recruitment burden and allows testing of the intervention in a variety of acute medical and surgical settings to ensure diverse geographical, unit size, and sub-speciality representation.

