## Assignment of interventions: allocation

### Sequence generation {16a}

Following eligibility assessment and consent, participants are randomised to either the dressing group or the routine care only group using a 1:1 ratio, permuted block sizes of four, six, and eight, stratified by hospital and division (i.e. medical or surgical).

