### Methods for additional analyses (e.g. subgroup analyses) {20b}

Post hoc subgroup analyses may be undertaken where there are differences between groups in relation to demographic and/or clinical characteristics.

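### The stated main relative risk and log-rank analyses omit the randomisation strata, and covariate adjustment and subgroup analysis are triggered by chance baseline differences

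*Protocol article*

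**What the plan says.** All quotes are from the protocol article.

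- Sequence generation {16a}: 1:1 allocation in "permuted block sizes of four, six, and eight, stratified by hospital and division". The trial design section {8} says the same. Study setting {9} gives three hospitals, so there are 3 × 2 = 6 strata.
- Statistical methods {20a}, main analysis: "Relative risk (RR) of HAPI for the intervention group compared to the control group will be computed and reported along with 95% confidence intervals", with P values. Time to injury gets a Kaplan-Meier curve, a log-rank test and a hazard ratio, with further Cox models for prognostic factors. Hospital and division appear in none of these.
- Statistical methods {20a}, adjustment: imbalance is called unlikely, with age, BMI and comorbidity count as examples. Then "if we find any differences, we will conduct adjusted analyses using multiple regression models".
- Statistical methods {20a}, centres: variability between hospitals is to be assessed, and "cluster-adjusted analysis will be carried out as a form of sensitivity analysis if required".
- Additional analyses {20b}: "Post hoc subgroup analyses may be undertaken where there are differences between groups in relation to demographic and/or clinical characteristics".

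**The concern.** The analysis should follow the randomisation. Stratified blocks remove between-stratum variation from the treatment comparison. An analysis that ignores the strata puts that variation back into the standard error.

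The adjustment rule is the stronger part of the point, because it is written down and is not merely a gap. With concealed individual randomisation, a baseline difference between arms is chance. It does not show that the unadjusted estimate is biased, and it is a poor guide to which covariates matter. The rule has no threshold and no closed covariate list, and it does not say whether the adjusted result replaces, supports or only accompanies the main relative risk. Two or more candidate answers could be on the table once the data are seen.

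The same trigger is misplaced for subgroups. A subgroup analysis asks whether the effect differs between kinds of patient, and imbalance between arms has no bearing on that.

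The cluster step has no stated criterion and does not fit the design. Patients are randomised individually within hospitals, so the three hospitals are strata, not randomised clusters. Whether the effect varies by hospital is a question for an interaction.

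**Working it through.** **1. The plan's own figure.** From Sample size {14}: 5% versus 10%, two-sided α 0.05, power 90%.

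n per group = (1.960 + 1.282)² × [0.05×0.95 + 0.10×0.90] / 0.05² = 10.507 × 0.1375 / 0.0025 = 577.9, so 578. This matches the protocol and is an unstratified two-proportion formula.

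**2. Cost of leaving out the strata.** Let p be the mean risk and V the variance of risk across six equal strata. With no treatment effect, the unstratified variance uses p(1−p), while the stratified variance uses p(1−p) − V. The ratio of standard errors is therefore 1/√(1 − V/[p(1−p)]).

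- Risks evenly spaced from 4% to 13% (the incidence range cited in {14}, used here as a between-stratum spread): p = 0.085, V = 0.000945, p(1−p) = 0.0778. V/[p(1−p)] = 0.0122 and the ratio is 1.006.
- Assumed wide spread of 2, 3, 5, 10, 15 and 25%: p = 0.10, V = 0.00647, p(1−p) = 0.09. V/[p(1−p)] = 0.0719 and the ratio is 1.038.

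A simulation agrees (40,000 trials per row, 1320 patients, six equal strata, near-balanced allocation; unstratified relative risk versus Mantel-Haenszel):

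| Control risks | True RR | SE of log RR, unstratified / stratified | Rejection rate, unstratified / stratified |
|---|---|---|---|
| all 10% | 1 | 0.166 / 0.166 | 4.8% / 4.8% |
| all 10% | 0.5 | 0.208 / 0.208 | 93.6% / 93.6% |
| 4–13% | 1 | 0.182 / 0.181 | 4.8% / 4.9% |
| 4–13% | 0.5 | 0.228 / 0.227 | 89.0% / 89.1% |
| 2–25% (assumed) | 1 | 0.166 / 0.160 | 4.0% / 4.7% |
| 2–25% (assumed) | 0.5 | 0.208 / 0.203 | 94.1% / 94.7% |

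Coverage of the 95% interval lies between 95.1% and 96.0% throughout. The unstratified interval is valid and slightly too wide.

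**3. How often the adjustment trigger fires.** The protocol gives no threshold. Assume that a difference means a baseline p below 0.05 on independent covariates. The chance of at least one is 1 − 0.95^k: 14% for k = 3, 26% for k = 6 and 40% for k = 10. Section {18a} lists more than ten recorded characteristics. Read literally, with any numerical difference counting, the trigger always fires and only the choice of covariates stays open.

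**4. What the trigger does to type I error.** This used a normal-approximation simulation of 400,000 null trials, with 3 or 10 covariates and covariate-outcome correlations of 0.10 to 0.30 (assumed).

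- A fixed conditional rule (adjust if triggered, then report that result): 4.3–4.9%.
- Free choice of the more favourable result after triggering: 5.3–5.7%.
- Unadjusted and fully adjusted conclusions disagree in 2.5–4.8% of null trials.

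**The case against.** The protocol never calls the main relative risk unadjusted, and the choice of estimator is commonly left to an analysis plan, which is not shown. That stands in part: silence on the strata is the weaker limb. It does not reach the imbalance trigger, the same trigger for subgroups or the conditional cluster step. These are affirmative statements, and an analysis plan could cure them only by departing from them.

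The adjusted analysis is not said to replace the main one, and a fixed conditional rule would not inflate type I error. Both are correct. The fault is that the rule is not fixed and the role of its result is not stated. The subgroup analyses are openly labelled post hoc and optional, which limits what they could be used to claim, but imbalance is still the wrong reason to run them.

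Two stronger readings are tempting. A reader might infer that the primary confidence interval is seriously wrong; the figures above show that it errs slightly on the safe side. A reader might also infer that the trial's inference rests on cluster adjustment with three hospitals. The text makes this a conditional sensitivity analysis and names no estimator, so it does not set the primary interval, and error rates for any particular cluster method cannot be charged to the plan.

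**Conclusion.** The point holds in a limited form. As stated, the main relative risk and log-rank analyses do not use the stratification factors. Covariate adjustment and subgroup analysis are prompted by chance differences, leaving a data-driven model and an adjusted result of undefined status.

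The size is modest. The standard error is about 0.5% too large over a 4–13% spread of stratum risks, and up to about 4% at the assumed 2–25%. The gain in power from stratifying, at a relative risk of 0.5, is 0.1 and 0.6 percentage points respectively. Type I error is about 5.3–5.7% only if the analyst chooses freely between results.

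These figures assume equal stratum sizes, a baseline p below 0.05 as the trigger and the correlations given above. The effect on the log-rank test was not computed; the argument there is one of principle. The change is worth making because it is cheap and removes a choice made after seeing the data, not because the planned result would otherwise be invalid.

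**What to change.** - **Primary analysis:** a relative risk adjusted for hospital and division, either Mantel-Haenszel over the six strata or modified Poisson regression with the strata as fixed effects. Stratify the log-rank and Cox analyses in the same way.
- **Adjusted analysis:** delete the imbalance trigger. Name one secondary model with a closed covariate list, fitted whatever the baseline table shows. Age, BMI and comorbidity count are natural candidates, with a stated rule for missing values, since {18a} accepts that weight or height may be undocumented. A pressure-injury risk score is not a ready candidate: {10} accepts either a Waterlow score or a yes/no judgement, and admits patients with neither on limited mobility, so there is no common score.
- **Centres:** replace the conditional cluster adjustment with a treatment-by-hospital interaction using fixed hospital effects. Treat it as descriptive: at the planned rates 578 × (0.05 + 0.10) ≈ 87 events are expected, or about 29 per hospital with equal recruitment.
- **Subgroups:** in {20b}, remove baseline imbalance as the reason for subgroup analyses.

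The cost is wording only, with no new data and no change to sample size. The changes should be dated before the statistician, who is blinded under {17a}, sees outcomes by group.

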### Trial design {8}

This study is a multi-site, parallel group, superiority RCT comparing the effectiveness of a prophylactic silicone foam border dressing in preventing sacral HAPI in hospitalised patients assessed at risk for PI. The unit of randomisation is eligible consenting patients who receive either the prophylactic sacral dressing or the routine care alone. Randomised to either the dressing group or the routine care only group is via a computer-generated 1:1 ratio, in varying permuted block sizes of four, six, and eight, stratified by hospital and division (i.e. medical or surgical).

All patients are followed for up to 14 days or until the trial endpoint, which is development of a new sacral HAPI, hospital discharge, or death—whichever occurs first. Patients who develop a HAPI in either arm are exited from the prevention trial and followed for an additional 14 days until discharge or death—whichever occurs first (up to a total of 28 days) to provide data on PI prevention and treatment costs. This will enable an extended economic evaluation that considers the benefits of prevention in terms of any reduced HAPI treatment costs or HLOS, alongside the costs of prevention.

An integral part of this study is its process evaluation. Process evaluations are particularly important for multi-site trials where it is necessary to determine whether interventions are implemented and received consistently across sites and to understand differences between them [17]. They also provide detailed documentation to enable replication, and information regarding the mechanism of action for significant or non-significant effects, thereby enhancing an intervention’s validity [16, 17].

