### Sample size {14}

The sample size is based on the effect size reported in published research [2]. HAPI cumulative incidence in similar settings ranged from 4 to 13% in The Border Trial [8]. We based calculations on an expected effect of intervention on the primary outcome, calculated using a cumulative incidence ratio of 0.5 (0.46 in our pilot trial) [13], between groups. This assumed a cumulative incidence of 5% in the intervention group compared to 10% in the control group. To obtain 90% power with a two-sided *α* level of 0.05, a total 578 patients per group are required. To allow for attrition, a further 10% will be recruited with a total sample of 1320 (*n* = 220 per group/site).

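### Kaplan-Meier curves for time to sacral HAPI, if discharge and death are censored, will overstate the absolute 14-day risk and risk difference relative to the primary cumulative incidence; the log-rank test and hazard ratio are not at fault.

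*Protocol article*

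**What the plan says.** In the protocol article, Trial design {8} follows patients for up to 14 days or "until the trial endpoint, which is development of a new sacral HAPI, hospital discharge, or death", whichever comes first. Plans for assessment and collection of outcomes {18a} repeats this rule.

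Statistical methods {20a} says of the primary outcome: "The main analysis will be based on comparisons of the cumulative incidence of pressure injuries in the two groups". The outcome is dichotomous and the arms are compared by relative risk, so a patient who is discharged or dies without an injury counts as a non-event.

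For the secondary endpoint, the same section says that time to HAPI "will be analysed using the Kaplan-Meier curve and log rank tests", and adds: "Hazard ratios along with 95% confidence intervals will be reported". Further Cox models are planned for prognostic factors.

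The article does not mention competing events or a cumulative incidence function, and it does not state how discharged or deceased patients enter the time-to-event analysis.

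**The concern.** Once a patient is discharged or dies, the trial can no longer observe a hospital-acquired injury in that patient. Discharge and death are therefore competing events and not ordinary loss to follow-up. Kaplan-Meier with these exits censored assumes that patients who left would have gone on to develop injuries in hospital at the same rate as those who stayed. The resulting curve describes a hospital that nobody leaves before day 14. The primary outcome describes the hospital as it is.

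The report could then show two 14-day figures per arm, the primary proportion and the height of the curve, with nothing to reconcile them. A reader who takes absolute risk or risk difference from the curve would overestimate both the burden of injury and the absolute benefit of the dressing. Eligibility requires an expected stay of only 24 hours or more, so exits before day 14 can be expected.

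**Working it through.** **Inputs from the article**
- Horizon: 14 days (Trial design {8}; Secondary outcomes).
- Event rates: "This assumed a cumulative incidence of 5% in the intervention group compared to 10% in the control group" (Sample size {14}).
- Recruitment: 1320 in total, so 660 per arm.

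**Input that has to be assumed**
- Length of stay after recruitment is not given. I take a constant daily exit hazard d (discharge or death), equal in both arms, with d = ln 2 / median stay, for medians of 3 to 10 days. The injury hazard h is also constant.

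**Step 1. The plan's own figure.** Sample size {14} states "a total 578 patients per group are required" for 90% power at two-sided 0.05. With unpooled variance: (1.960 + 1.282)² × (0.10 × 0.90 + 0.05 × 0.95) / 0.05² = 577.9, that is 578. The figure reproduces. It rests on proportions and is untouched by what follows.

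**Step 2. Find the injury hazard that yields the planned 14-day proportion.** Solve

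h / (h + d) × (1 − exp(−14(h + d))) = 0.10 (control) or 0.05 (dressing).

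Example with a median stay of 5 days: d = 0.6931 / 5 = 0.1386.
- Control: h = 0.0176. Check: 0.0176 / 0.1562 × (1 − exp(−2.187)) = 0.100.
- Dressing: h = 0.00843. Check: 0.00843 / 0.1471 × (1 − exp(−2.059)) = 0.050.

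**Step 3. What Kaplan-Meier would show with exits censored.** 1-KM(14) = 1 − exp(−14h).
- Control: 1 − exp(−14 × 0.0176) = 21.8%.
- Dressing: 1 − exp(−14 × 0.00843) = 11.1%.
- Cause-specific hazard ratio: 0.00843 / 0.0176 = 0.48.

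**Step 4. Range over the assumed stay.** The true values are 10% and 5%, risk difference 5 points, relative risk 0.50.

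| Assumed median stay | 1-KM control | 1-KM dressing | Difference (points) | Ratio of 1-KM | Cause-specific HR |
|---|---|---|---|---|---|
| 10 days | 15.4% | 7.8% | 7.7 | 0.50 | 0.48 |
| 7 days | 18.1% | 9.1% | 8.9 | 0.51 | 0.48 |
| 5 days | 21.8% | 11.1% | 10.7 | 0.51 | 0.48 |
| 4 days | 25.2% | 13.0% | 12.3 | 0.51 | 0.48 |
| 3 days | 31.0% | 16.2% | 14.8 | 0.52 | 0.48 |

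The absolute level rises by a factor of about 1.5 to 3. The relative measures barely move.

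**Step 5. Patients left at the end of the curve.** 660 × exp(−14(h + d)) at a 5-day median gives about 74 in control and 84 in the dressing arm. The tail would be imprecise as well as too high. This count also depends on the assumed stay.

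**Step 6. Does the proposed estimator agree with the primary outcome?** In simulated trials with 660 per arm, 400 runs per setting and mean times to exit of 4, 5, 7 and 10 days, the Aalen-Johansen estimate at day 14 averaged about 10.0% and 5.0% and equalled the crude proportion. Kaplan-Meier in the same data matched the formula in Step 3 (for a mean of 5 days, 27.9% simulated and 27.9% by formula in control).

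**Step 7. If discharge differs between arms.** Take identical injury hazards (h = 0.0176) and median stays of 5 and 4 days. Cumulative incidence is then 10.0% and 0.0176 / 0.1909 × (1 − exp(−14 × 0.1909)) = 8.6%, a relative risk of 0.86 with a hazard ratio of 1.0. This is hypothetical. The economic evaluation does, however, allow for a between-group difference in length of stay, and only a discharge hazard ratio would let a reader explain such a gap.

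**The case against.** The strongest case against the point is that nothing inferential is wrong. Time to HAPI is a secondary endpoint compared by log-rank test and hazard ratio. With discharge and death censored, both validly address the cause-specific hazard, that is, the rate of injury among patients still in hospital. The article nowhere says that the height of the Kaplan-Meier curve will be reported as 14-day risk, and it also plans a rate per 1000 bed days. This stands, and it confines the point to the curve and to any absolute risk read from it.

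A reader might infer that the curves would contradict the primary result. The documents do not support that. The two quantities answer different questions, and with similar discharge in both arms they agree in direction and closely in relative size. The mismatch is in absolute level and risk difference.

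A reader might also infer that the curve would be about twice the primary figure. That is close to the 5-day case only. No length of stay is given, so only the range can be stated.

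Finally, the censoring rule is not written down, and such rules are often left to an analysis plan. If event-free patients were carried forward to day 14, the overstatement would vanish. The stated end of follow-up makes censoring at discharge the natural reading, and the article does name the estimator, so the point does not rest on silence alone.

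**Conclusion.** The point holds in a limited form. Kaplan-Meier is a named estimator that does not fit an endpoint whose follow-up stops at discharge or death. With those exits censored, its direction of error is certain: the curve overstates the absolute 14-day risk in each arm, and under the assumptions above it also overstates the risk difference. The size is not certain. For median stays of 10 to 3 days, the planned 10% would appear as about 15% to 31%, the planned 5% as about 8% to 16%, and the 5-point difference as about 8 to 15 points. These figures assume constant hazards and equal exit rates in both arms.

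The primary analysis, the sample size, the log-rank test and the Cox model are unaffected. The documents do not support a claim that the treatment comparison itself is biased or that the log-rank test must be replaced.

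**What to change.** In the analysis of time to HAPI:

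1. Replace the Kaplan-Meier curve with Aalen-Johansen cumulative incidence curves by arm, treating discharge alive and death as competing events. The day-14 value then matches the primary proportion when outcomes are complete.
2. Keep the log-rank test and the Cox model, state that discharge and death are censored in them, and label the hazard ratio as cause-specific.
3. Report the cause-specific hazard ratio for discharge beside it, so that any difference in length of stay between arms is visible.

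Gray's test may be added but is optional, because the primary relative risk already compares cumulative incidence.

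Cost: a few sentences of wording, and possibly software other than SPSS V24 for the curve. Injury, discharge and death are already recorded, so no new data are needed.
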